## Abstract

**Introduction:**

Chronic postsurgical pain (CPSP) remains a major clinical challenge following total knee arthroplasty (TKA), with psychological maladaptation and persistent neuromuscular dysfunction considered key contributors to ongoing pain and disability. Pain neuroscience education (PNE) may improve maladaptive pain cognitions, whereas blood flow restriction training (BFRT) can enhance muscle function and induce exercise-related hypoalgesia. Although both interventions have shown potential benefits in chronic pain rehabilitation, no randomized controlled trial has investigated the combined efficacy of these two interventions in patients with CPSP after TKA. This study aims to determine whether combined PNE + BFRT produces greater improvements in pain and function in this population.

**Methods and analysis:**

This study is a single-blind, four-arm, parallel-group randomized controlled trial. A total of 148 participants will be randomly assigned (1:1:1:1) to the Control, PNE, BFRT, or combined PNE + BFRT group. PNE will be delivered in two structured sessions. BFRT involves a 12-week supervised low-load resistance training program. The primary outcome is the group-by-time interaction effect on KOOS₄ over time. Secondary outcomes include pain intensity (NRS), global perceived effect, pain distribution, psychological measures (HADS, PCS), physical performance (40-m fast-paced walk test, stair climb test, and 30-s chair stand test), and neuromuscular strength. Assessments will be conducted at baseline, post-intervention (12 weeks), and at 12-week, 24-week, and 36-week follow-ups. Data will be analyzed using linear mixed-effects models under the intention-to-treat principle.

**Ethics and dissemination:**

Ethics approval has been obtained from the Ethics Committee of the Chengdu Sport University, with permission number CDSUEC2026- 177. This study has been registered with the Chinese Clinical Trial Registry (ChiCTR2600125544). Written informed consent will be obtained from all participants prior to enrollment.

**Trial registration number:**

Chinese Clinical Trial Registry ChiCTR2600125544, registered on May 28, 2026.

**Supplementary Information:**

The online version contains supplementary material available at https://doi.org/10.1186/s13018-026-07146-y.

## Introduction

Knee Osteoarthritis (KOA) is a prevalent degenerative joint disease and a leading cause of disability worldwide [1, 2]. Total knee arthroplasty (TKA) is currently recognized as the preferred treatment for end-stage KOA [3]. Despite substantial improvements in pain and function following surgery, approximately 20% of patients continue to experience persistent moderate-to-severe pain lasting beyond three months postoperatively, commonly referred to as chronic postsurgical pain (CPSP) [4–6].

CPSP is not only associated with an increased risk of opioid dependence but also creates a substantial socioeconomic burden [7, 8]. Additionally, inadequately managed CPSP may precipitate comorbidities such as insomnia and hypertension [9], undermining surgical expectations and exacerbating doctor-patient conflicts [10]. Given the challenges and high cost of CPSP treatment, coupled with the poor efficacy of pharmacological prophylaxis [11–13], exploring efficient and safe treatment strategies is of significant clinical and societal urgency. The genesis and development of CPSP are multifactorial. Among these predictors, psychological factors are widely regarded as key predictors of CPSP [14–17]. Patients' emotional responses to pain profoundly influence their recovery trajectory, especially Pain Catastrophizing (PC), a maladaptive cognitive pattern, involving rumination, magnification, and helplessness, has been consistently confirmed as a potent, independent risk factor for CPSP [18–20].

Pain Neuroscience Education (PNE) has emerged as a prominent intervention for pain management. By emphasizing that pain is not strictly a direct signal of tissue damage, it effectively helps patients re-evaluate the nature of pain [21–25]. Clinically, PNE has proven effective in reducing pain intensity and significantly alleviating fear-avoidance beliefs, pain catastrophizing, and anxiety in chronic pain populations [22, 26, 27]. However, while PNE has beneficial effects on pain-related cognition and emotional factors, its effects on physical function and muscle performance remain relatively limited [28–30]. Therefore, PNE is optimally deployed as part of a multimodal treatment strategy, integrated with other interventions to elicit synergistic effects and deliver superior clinical outcomes.

Research indicates that therapeutic exercise can attenuate pain sensitivity in both motor and non-motor areas [31–33]. As exercise intensity and duration increase, the effect of inducing pain reduction becomes increasingly pronounced [34–36]. However, for patients with CPSP following TKA, engaging in prolonged high-intensity exercise may pose significant challenges. Blood Flow Restriction Training (BFRT) is a low-intensity training method that partially restricts arterial blood flow and blocks venous return by applying external pressure to the proximal end of the limb [37]. Emerging evidence suggests that BFRT can produce muscle hypertrophy, strength gains, and analgesic effects comparable to those achieved with high-intensity resistance training while imposing substantially lower mechanical stress on the joint [38–40]. Nevertheless, BFRT primarily targets physical and neuromuscular impairments and may not adequately address maladaptive pain-related cognition or fear-avoidant behaviors.

Accordingly, combining PNE with BFRT may offer a complementary rehabilitation strategy. PNE may enhance psychological readiness for rehabilitation by reducing pain-related fear, catastrophizing, and perceived threat associated with movement, whereas BFRT may promote functional recovery and pain relief. To date, no randomized controlled trial has investigated whether combining PNE and BFRT provides superior clinical benefits in patients with established CPSP following TKA. Therefore, this study is designed as a Randomized Controlled Trial to compare the effects of Control, PNE, BFRT, and combined PNE + BFRT on pain, psychological outcomes, physical performance, and knee-related function in patients with CPSP after TKA. We hypothesize that participants receiving the combined PNE + BFRT intervention will demonstrate greater improvements in knee-related function, pain intensity, psychological outcomes, and physical performance compared with those receiving either intervention alone or usual care.

## Method and analysis

### Study design

The study is designed as a single-center, four-arm, parallel-group, superiority randomized controlled trial. A total of 148 participants will be recruited from the Chengdu Sport University. All therapeutic interventions and data collection will be conducted at the School of Sports Medicine and Health, Chengdu Sport University.

Potential participants will be targeting individuals who underwent unilateral TKA at least one year prior. Eligible candidates will be contacted by telephone for preliminary screening. Those meeting eligibility criteria will be invited for an in-person baseline assessment and receive a comprehensive explanation of the study procedures. Written informed consent will be obtained before enrollment. A screening log will be maintained to document eligibility and reasons for exclusion. Participants will be consecutively recruited until the required sample size (n = 148) is achieved. Participants will be randomly assigned in a 1:1:1:1 ratio to one of four groups: the Control group, the PNE group, the BFRT group, or the PNE combined with BFRT group.

The study has received approval from the Ethics Committee of the Chengdu Sport University (Committee Reference Number: CDSUEC2026- 177) and is registered with the Chinese Clinical Trial Registry (Registration Number: ChiCTR2600125544). The trial will be conducted in accordance with the Declaration of Helsinki. Any protocol amendments will be promptly submitted to the Ethics Committee and updated in the trial registry. Given the low-risk nature of the interventions, an independent data monitoring committee will not be established. However, all adverse events will be recorded and monitored throughout the trial. Any serious adverse events (SAEs) will be immediately reported to the Ethics Committee.

The study period will span from May 2026 to July 2029. Participant recruitment will occur between May 2026 and July 2027. Follow-up assessments will be completed by July 2029. The study protocol was developed in accordance with the SPIRIT 2025 Statement, as shown in Fig. 1. The timeline for participant enrollment, interventions, assessments, and follow-up visits is detailed in Table 1.

**Fig. 1 Fig1:**
[figure not shown]
Study flow diagram

**Table 1 Tab1:** Schedule of the process of trial

Period	Screening	Intervention			Follow-up		
Time point	Week 0	Week 0	Week 6	Week 12	Week 24	Week 36	Week 48
Eligibility	×						
Informed consent	×						
Allocation							
Control group		———————————————————————————————————————————————————					
PNE group		×	×				
BFRT group		———————————————————————————————————————————————————					
PNE + BFRT group		———————————————————————————————————————————————————					
KOOS₄		×		×	×	×	×
KOOS		×		×	×	×	×
NRS		×		×	×	×	×
GPE		×		×	×	×	×
Pain Extent and Distribution		×		×	×	×	×
HADS		×		×	×	×	×
PCS		×		×	×	×	×
40 m-FPWT		×		×	×	×	×
SCT		×		×	×	×	×
30CST		×		×	×	×	×
Muscle strength		×		×	×	×	×
Adverse events		————————————————————————————————————————————————————————————————————————————————————					
Dropout reasons		————————————————————————————————————————————————————————————————————————————————————					

PNE, Pain Neuroscience Education; BFRT, Blood Flow Restriction Training; KOOS, Knee Osteoarthritis Outcome Score; NRS, Numerical Rating Scale; GPE, Global Perceived Effect; HADS, Hospital Anxiety and Depression Scale; PCS, Pain Catastrophizing Scale; 40 m-FPWT, 40-m Fast-Paced Walk Test; SCT, Stair Climb Test; 30CST,30-s Chair-Stand Test.

### Inclusion criteria

Participants meeting all of the following inclusion criteria will be enrolled:Adults who have undergone primary TKA for KOA with a postoperative period of ≥ 12 months.Presence of persistent pain in the target knee for a duration of > 6 months.Pain localized to the surgical site or its corresponding nerve distribution, with other potential causes excluded (e.g., prosthesis loosening, infection).An average pain intensity score of ≥ 4 points on the Numerical Rating Scale (NRS) over the week preceding enrollment (0 indicates no pain, 10 indicates the most severe pain, and ≥ 4 indicates moderate to severe pain).Stable vital signs, clear consciousness, and sufficient cognitive and linguistic ability to assess their own pain and cooperate in completing pain assessment scales.

### Exclusion criteria

Participants presenting with any of the following will be excluded:Specific reasons for chronic pain, such as loosening and failure of the prosthesis, which requires revision surgery.Secondary osteoarthritis associated with rheumatoid arthritis or sequelae of previous trauma.Recent surgical history involving the index knee within 3 months or significant injury within the preceding 12 months.Confounding pain patterns, defined as acute pain in areas other than the index knee during baseline testing.Vascular contraindications, including a history of deep vein thrombosis, peripheral vascular disease, or active bleeding diathesis incompatible with compression training.Concurrent medication or trial participation, specifically the use of opioid analgesics within 2 weeks or enrollment in other pain-related studies.General ineligibility due to pregnancy, lactation, severe cognitive impairment, or inability to provide informed consent.

### Randomization and blinding

Participants will be randomly assigned in a 1:1:1:1 ratio to the Control, PNE, BFRT, or combined PNE + BFRT groups using a computer-generated randomization sequence created in SPSS 27.0 (IBM SPSS, Armonk, NY, USA) by an independent researcher not involved in recruitment, assessment, or intervention delivery. To ensure balance across groups while minimizing allocation predictability, permuted block randomization with randomly varying block sizes of 4 and 8 will be implemented. The allocation sequence will be concealed using a centralized, password-protected system accessible only to the trial coordinator, who will not be involved in participant recruitment, intervention delivery, outcome assessment, or data analysis.

Following completion of baseline assessment and confirmation of eligibility, the trial coordinator will assign participants to the corresponding intervention according to the pre-generated randomization sequence. Due to the nature of the interventions, blinding of participants and treating therapists is not feasible. Therefore, this trial will employ blinded outcome assessment and blinded statistical analysis. Outcome assessments will be conducted by trained assessors who are not involved in randomization or intervention delivery, and data analysts will remain blinded to group allocation throughout the study period. Participants will be instructed not to disclose their group allocation during assessment sessions to minimize the risk of unblinding. Statistical analyses will be performed using de-identified datasets with masked group codes to further reduce analytical bias.

### Sample size

The sample size was estimated using G*Power software (version 3.1.9.7, Franz Faul, Universität Kiel, Germany). The primary outcome is the KOOS₄ score (mean score of the Pain, Symptoms, Activities of Daily Living, and Knee-Related Quality of Life subscales) from the Knee Osteoarthritis Outcome Score (KOOS). Based on previous research, a 10-point improvement in KOOS₄ was considered the Minimum Clinically Important Difference (MCID), with an anticipated Standard Deviation (SD) of 15 points [41, 42]. The following parameters were utilized for the sample size calculation: Significance Level (α) = 0.05, Statistical Power (1-β) = 0.90, Effect Size (Cohen's f) = 0.34, and Number of Groups = 4. The calculations indicated that the minimum total sample size required to detect this effect was 128 cases. Considering an anticipated attrition rate of approximately 15% and to ensure equal and balanced allocation across four groups, the total sample size was increased to 148 participants, resulting in 37 participants per group. This approach enhances the stability and reliability of the study results, ensuring that the research objectives will be successfully met.

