### Primary outcome

#### KOOS_4_

The primary outcome is the between-group difference in longitudinal change in KOOS₄ across all assessment time points. KOOS_4_ was selected as the primary outcome measure because persistent CPSP after TKA affects not only pain intensity but also broader dimensions of knee-related symptoms, activities of daily living, and quality of life, making patient-centered assessment essential when evaluating treatment outcomes. It is one of the most widely used and validated assessment tools in patients undergoing TKA [28].

The KOOS₄ is calculated as the mean of four KOOS subscales (Pain, Symptoms, Activities of Daily Living, and Knee-Related Quality of Life), excluding the Sport/Recreation subscale. Scores range from 0 to 100, with higher scores indicating better knee-related function [47, 48]. Based on prior literature, A between-group difference of 10 points is considered the MCID and will be used to interpret the clinical relevance of observed effects [42].

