### Statistical analysis

All statistical analyses will be conducted using SPSS version 27.0 (IBM Corp., Armonk, NY, USA) by statisticians blinded to group allocation. All tests will be two-tailed with a significance level set at *P* < 0.05. Baseline characteristics will be summarized using descriptive statistics. Continuous variables will be presented as mean ± standard deviation (SD) or median (interquartile range), depending on data distribution. Categorical variables will be expressed as frequencies and percentages. All efficacy analyses will follow the intention-to-treat (ITT) principle. The primary analysis will focus on evaluating whether the longitudinal response trajectory of the combined PNE + BFRT group differs from those of the comparison groups over time. To address this objective, linear mixed-effects models (LMMs) will be used for repeated-measures analyses of the primary and secondary outcomes. The primary inference of interest will be based on the group-by-time interaction effect, which reflects differential changes in outcome trajectories between intervention groups throughout the study period. To reduce the risk of type I error inflation, KOOS₄ will be considered the sole confirmatory primary outcome, while all other outcomes will be treated as secondary or exploratory. If a significant group-by-time interaction is identified for KOOS₄, post-hoc pairwise comparisons with Bonferroni correction will be performed. Secondary outcomes will be analyzed using similar mixed-effects modeling approaches. Estimated marginal mean differences with 95% confidence intervals will be reported where appropriate. Missing data will be assumed to be missing at random and handled using maximum likelihood estimation within the mixed-effects modeling framework. A supplementary per-protocol analysis, including participants with at least 80% adherence to the intervention, may also be conducted.

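### Cohen's f = 0.34 does not follow from a 10-point difference and SD 15 in four equal arms, so the stated 90% power at 128 analysed depends on arm means that the protocol does not state

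*Protocol article*

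**What the plan says.** The Sample size section states that "a 10-point improvement in KOOS₄ was considered the Minimum Clinically Important Difference (MCID"), "with an anticipated Standard Deviation (SD) of 15 points". It then lists the G*Power inputs: "Significance Level (α) = 0.05", "Statistical Power (1-β) = 0.90", and the effect size as "f) = 0.34, and Number of Groups = 4". The result is a minimum of 128, raised to 148 (37 per arm) for about 15% attrition.

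The section does not say how 0.34 was obtained from 10 and 15, or which four arm means are assumed. The Primary outcome section (KOOS₄) treats the 10 points as a contrast between arms: "A between-group difference of 10 points is considered the MCID and will be used to interpret the clinical relevance of observed effects". It does not say which arms. The Introduction hypothesises that the combined arm does better "compared with those receiving either intervention alone or usual care". The Statistical analysis section bases the primary inference on the group-by-time interaction in a linear mixed model.

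**The concern.** With four arms, f is the standard deviation of the four true arm means divided by the within-arm SD. One difference of 10 points does not determine it; the positions of the other arms matter. The value 0.34 is very close to d/2 = (10/15)/2 = 0.333, which is the conversion for two groups. In four equal arms, d/2 is correct only when two arms sit at the top and two at the bottom. The combined arm would then be level with another arm, which is not what the Introduction hypothesises.

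At stake is how the result will be read. The protocol attaches 90% power to a 10-point difference and uses the same 10 points to judge clinical relevance. A non-significant result could therefore be taken as good evidence against a 10-point benefit, on the strength of a power figure that the stated inputs do not support.

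**Working it through.** **Inputs (protocol article).** Difference 10 points, SD 15, f = 0.34, four groups, alpha 0.05, power 0.90, minimum N 128 and randomised N 148, all from Sample size. Equal allocation is from Randomization and blinding.

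**Step 1: reproduce the plan's figure.** For a one-way ANOVA, power is the upper tail of a noncentral F with 3 and N − 4 degrees of freedom and noncentrality λ = N·f². With f = 0.34 and N = 128, λ = 128 × 0.1156 = 14.80 and power is 90.4%. The smallest N with at least 90% is 127, or 128 in equal arms. This matches the stated 128. The G*Power repeated-measures options, with an assumed five time points and correlation 0.5, give 78 (between) and 22 (within-between), so the one-way four-group test is the variant that fits.

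**Step 2: where 0.34 could come from.** d = 10/15 = 0.667 and d/2 = 0.333. If d is first rounded to 0.67, d/2 = 0.335, which rounds to 0.34.

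**Step 3: f for four equal arms.** f = (SD of the four means, divisor 4)/15. For example, means 0/0/0/10 have average 2.5 and squared deviations 3 × 6.25 + 56.25 = 75. Then √(75/4) = 4.33 and f = 4.33/15 = 0.289.

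| Arm means (points above lowest arm) | SD of means | f | λ at 128 | Power, 128 | Power, 148 | N for 90%, equal arms |
|---|---|---|---|---|---|---|
| 0 / 5 / 5 / 10 | 3.54 | 0.236 | 7.11 | 58.2% | 65.4% | 260 |
| 0 / 0 / 0 / 10 | 4.33 | 0.289 | 10.67 | 77.6% | 84.0% | 176 |
| 0 / 0 / 10 / 10 | 5.00 | 0.333 | 14.22 | 89.1% | 93.4% | 132 |
| 0 / 3.7 / 3.7 / 13.7 | 5.09 | 0.340 | 14.76 | 90.3% | about 94% | 128 |
| 0 / 10 / 10 / 20 | 7.07 | 0.471 | 28.44 | 99.7% | 99.9% | 68 |

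The first and third rows are the minimum and maximum of f when the largest difference is 10 points.

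**Step 4: the spread that f = 0.34 needs.** The SD of the means must be 0.34 × 15 = 5.1 points. For a given range the SD of four means is at most half the range, so the range must be at least 10.2 points. That minimum applies only to a two-and-two split. If the combined arm is 10 points above both single arms and these are x above Control, f rises from 0.289 at x = 0 to about 0.34 at x = 3.7 and 0.363 (power 94.0%) at x = 5.

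**Step 5: sensitivity to the analysis.** The rows above concern one time point without baseline adjustment. As an illustration only, adjust for a baseline score with assumed correlation r, so that f becomes f/√(1 − r²). With 128 analysed and r = 0.3, 0.5 and 0.7, power is 82%, 89% and 98% for 0/0/0/10, and 63%, 72% and 88% for 0/5/5/10. The protocol gives no correlation.

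**The case against.** The strongest reply is that the calculation contains no error at its own inputs, since f = 0.34 does give 128, and that nothing in the protocol caps the spread at 10 points. If 10 points is the combined arm's margin over each single intervention, and these are modestly better than Control, f = 0.34 is reached and exceeded. The article's own rationale expects some benefit from PNE and from BFRT alone. This stands: 90% is attainable under a pattern consistent with the hypothesis. But the protocol does not state that pattern, and the two numbers it offers as the basis do not yield 0.34.

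A reader might go further and infer three things that the documents do not support:

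- **That the two-group conversion was used by mistake.** The numerical match is close, but no derivation is given, so this remains an inference. The mismatch between 10, 15 and 0.34 does not depend on it.
- **That the trial's power is 78%, or 58% because effects are additive.** Each figure belongs to one chosen pattern. The 58% assumes 5 points per component; additive effects of 10 points each give 99.7%.
- **That the primary analysis is underpowered.** The primary test is a group-by-time interaction in a mixed model. Its power depends on within-person correlations that the article does not give, and Step 5 shows how far these can move the figure.

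**Conclusion.** The point holds as a mismatch between the stated inputs and the stated effect size. Assuming equal arms, SD 15, 10 points as the largest difference between arms and a one-way ANOVA at one time point, f cannot exceed 0.333, and power with 128 analysed is 58% to 89%. It is 78% if only the combined arm differs. In the most favourable of these patterns the shortfall is small: 89.1% against 90%, or 132 participants against 128. In the least favourable it is large. The protocol does not say which pattern it assumes, so the unqualified 90% for a 10-point difference is unsupported. It has not been shown to be wrong for every pattern compatible with the hypothesis.

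**What to change.** Keep N = 148. In the Sample size section:

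1. State the four assumed arm means, the time point they refer to, and the f they imply with SD 15. Say which arms the 10-point difference separates.
2. Replace the unqualified 90% with power conditional on that pattern. Possible wording: *If only the combined arm differs, by 10 points (SD 15), f = 0.289 and power is 78% with 128 analysed and 84% with 148. Over all patterns with a largest difference of 10 points, power is 58% to 89% with 128 and 65% to 93% with 148.* If a wider spread is intended, state and justify it.
3. Add that these figures are for a one-way ANOVA at one time point, not for the planned group-by-time interaction. If power for the interaction is also given, state the assumed correlations and the mean trajectories.

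The cost is wording only: no extra participants and no change to arms, outcome or analysis. The drawback is that the stated power becomes less favourable, unless a wider spread of means can be justified.

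### The 90% power and N = 128 belong to a four-group one-way ANOVA at one time point; no power is given for the planned interaction or the Bonferroni-corrected pairs

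*Protocol article*

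**What the plan says.** The Sample size section of the protocol article names G*Power and gives these inputs: "Significance Level (α) = 0.05", "Statistical Power (1-β) = 0.90", and a Cohen's f of "0.34, and Number of Groups = 4". It cites a 10-point KOOS₄ difference and an SD of 15. It then concludes: "The calculations indicated that the minimum total sample size required to detect this effect was 128 cases". The number is raised to 148 (37 per arm) for about 15% attrition. The section closes by saying that this size secures the trial's objectives.

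The Statistical analysis section plans something else. There, "linear mixed-effects models (LMMs) will be used for repeated-measures analyses of the primary and secondary outcomes", and the primary inference is the group-by-time interaction. If that is significant for KOOS₄, "post-hoc pairwise comparisons with Bonferroni correction will be performed". The Outcomes section lists five assessments (baseline and weeks 12, 24, 36 and 48).

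The substantive claim is pairwise. The Introduction hypothesises that the combined arm does better than either single intervention or usual care. The Discussion ties clinical application to the combined arm outperforming the single-intervention arms. The Primary outcome section defines the 10-point MCID as a between-group difference.

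**The concern.** A power statement is useful only if it refers to the test that will be run and the effect that will be claimed. Here the listed inputs contain no number of measurements, no correlation between them and no allowance for Bonferroni correction, although the analysis involves all three. The 90% appears to describe neither the confirmatory interaction nor any comparison of the combined arm with another arm.

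What is at stake is interpretation. If a combined-versus-single comparison is not significant, a reader who trusts the 90% may take it as good evidence of no added benefit. That assurance was never calculated.

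**Working it through.** **Inputs.** From Sample size: alpha 0.05, power 0.90, f = 0.34, four groups, difference 10, SD 15, 128 evaluable (32 per arm), 148 randomised (37 per arm), about 15% attrition. From Statistical analysis: two-sided tests, interaction, Bonferroni pairs. From Outcomes: five assessments. Assumed, because not in the article: within-person correlation ρ of 0.3, 0.5 or 0.7 with compound symmetry; three pairs (combined against each other arm) or six (all pairs); SD 15 as the SD of a score at one visit.

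**1. The plan's own figure.** One-way ANOVA, λ = f²N = 0.34² × 128 = 14.80, df 3 and 124. Power is 0.904. The smallest N reaching 0.90 is 127, rounded to 128 for four equal arms. Repeated-measures versions with f = 0.34, five times and ρ = 0.5 give 80 (between factors) or 24 (within-between interaction), not 128. The stated 90% is therefore that of the one-way test.

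**2. The effect pattern behind f.** The article does not show how f was obtained. With a spread of 10 between the best and worst arm and SD 15:
- Two arms at 10, two at 0: f = 5/15 = 0.333. This is the largest value possible with that spread and is close to 0.34.
- Only the combined arm at 10: SD of the four means = 10 × √(0.25 × 0.75) = 4.33, so f = 4.33/15 = 0.289. ANOVA power at 128 is 0.78.
- Arms at 0/5/5/10: SD of means = √12.5 = 3.54, so f = 0.236. ANOVA power at 128 is 0.58.

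In the first pattern the combined arm necessarily ties with one other arm, which is not the stated hypothesis.

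**3. Pairwise power at one visit, baseline not used.** d = 10/15 = 0.667, noncentrality d√(n/2), which is 2.67 at n = 32 and 2.87 at n = 37. Two-sided t test at 0.05/m:

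| Pairs m | 32 per arm | 37 per arm |
|---|---|---|
| 1 (no correction) | 0.75 | 0.81 |
| 3 | 0.58 | 0.66 |
| 6 | 0.48 | 0.56 |

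A 15% loss from 148 leaves 148 × 0.85 = 125.8, or about 31 per arm. This barely changes the result (0.46 with six pairs).

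**4. Pairwise power for the average of four follow-ups minus baseline, 32 per arm.** Variance factor v = (1 + 3ρ)/4 + 1 − 2ρ, which is 0.875, 0.625 and 0.375 at ρ = 0.3, 0.5 and 0.7. Then d = 10/(15√v) = 0.713, 0.843 and 1.089.

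| Pairs | ρ = 0.3 | ρ = 0.5 | ρ = 0.7 |
|---|---|---|---|
| 3 | 0.65 | 0.82 | 0.97 |
| 6 | 0.55 | 0.74 | 0.94 |

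**5. The interaction, N = 128.** df1 = 3 × 4 = 12, df2 = 124 × 4 = 496, λ = 32 × SS/(15²(1 − ρ)). SS is the sum of squared interaction effects for a gain sustained over all four follow-ups.

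| Gains by arm | SS | ρ = 0.3 | ρ = 0.5 | ρ = 0.7 |
|---|---|---|---|---|
| Two arms gain 10 | 80 | 0.76 | 0.91 | 0.99 |
| Combined only gains 10 | 60 | 0.60 | 0.78 | 0.97 |
| 0/5/5/10 | 40 | 0.40 | 0.56 | 0.83 |

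**The case against.** Sizing on a simple omnibus test and then fitting a mixed model is common, and it need not leave a trial short. Repeated measures can add precision. If two arms gain a sustained 10 points, the pattern closest to the stated f, the interaction keeps 0.91 at ρ = 0.5. With averaging over follow-ups and ρ = 0.7, even six-pair Bonferroni comparisons reach 0.94. The pairwise tests are also described as post hoc and conditional on the interaction, which carries the primary inference.

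All of this stands, and it limits what can be said about size. A reader might infer that each decisive comparison has about 50% power. That figure needs four choices at once: six pairs, 32 completers per arm, one visit and no use of baseline. The article fixes neither the family size nor the visit, and it defines the primary outcome as change across all time points. Three pairs is at least as natural a reading, since the stated question sets the combined arm against the other groups. Nor do the documents make beating both single arms a formal success criterion, so a joint probability for that event should not be presented as the trial's power.

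The objection does not rescue the 90% as stated. It holds only for particular correlations and patterns, and the article commits to none of them. This is not merely detail left to an analysis plan: the article attaches a specific power figure to a test it does not plan to run.

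**Conclusion.** The concern holds as a mismatch between the power statement and the analysis. That 128 and 90% are those of a one-way ANOVA is established by exact reproduction. That this is neither the planned interaction nor the Bonferroni pairs follows from the article's own text.

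The size of the shortfall is only a range. At one visit with SD 15 and no use of baseline, every pairwise figure is below 0.90, even without correction. Once change, averaging and correlation enter, pairwise power can fall short of 0.90 or exceed it. Interaction power depends as much on the effect pattern as on the correlation. The documents do not support a flat statement that the trial is underpowered; they support the statement that its power for its own question is unknown. Confidence is high on the mismatch and moderate on its magnitude, which rests on compound symmetry, a sustained effect and ρ between 0.3 and 0.7.

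**What to change.** Replace the ANOVA power statement with the power of (a) the planned group-by-time interaction and (b) the combined-versus-comparator contrasts at the Bonferroni alpha actually used. Give both at 148 randomised and after 15% attrition. State the assumed pattern of effects across the four arms, the within-person correlation as a range, whether the contrast is at one visit or an average, and the number of pairs. Say explicitly that the 90% does not apply to the Bonferroni-adjusted pairs. Drop or soften the closing assurance that the sample size secures the objectives.

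The new figure must match the planned analysis. For example, a baseline-adjusted week-12 contrast at an uncorrected 0.05 with ρ = 0.5 gives d = 0.667/√(1 − 0.25) = 0.770 and power 0.86 at 32 per arm. That should not be quoted as this trial's power: the article plans neither a week-12-only contrast nor an uncorrected alpha, and it does not specify baseline adjustment. At 0.05/6 the same contrast has 0.64.

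The cost is one recalculation and one rewritten paragraph, with no extra patients. The stated power may come out lower.
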